#### Secondary outcomes

HIV-related outcomes include viral suppression (VL) using dried blood spots and adherence will be assessed using the Adolescent Master Protocol questionnaire, an adaptation of a self-reported adherence questionnaire that measures the number of missed doses. We will also assess the validity of these scales in our study population. Mental health and well-being outcomes will be assessed using the PHQ-9,^78 79^ GAD-7,^80 81^ Patient-Reported Outcomes Information System Sleep Disturbance Scale,^82 83^ Child and Youth Resilience Measure^84 85^ and Personal Well-Being Score.^86^

### Sample size

One of the areas of focus addressed by feasibility studies is the reach (uptake) of an intervention by the intended audience.^73^ Reach considers the absolute number, proportion and representativeness of the target population willing to participate in a given intervention and the reasons why or why not.^87^ Feasibility studies are not expected to have large sample sizes; therefore, a precision estimate was made for our sample size.^74 88^ If the true proportion of those willing to enrol (reach) is 75%, a sample size of 67 approached and 50 enrolled would allow us to estimate this proportion with a precision of ±10%. If 90% of participants complete the study at 6 months, a sample size of 50 ALHIV will allow us to estimate adoption (participant retention) with a precision of ±8%.

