ALHIV are disproportionately affected by and experience mental and behavioural health problems at higher rates than their non-HIV counterparts.^9 17^ Studies carried out in South Africa have found high rates of mental health problems, at a prevalence of 8%–12%,^18^,^20^ with increased engagement in risky behaviours among ALHIV.^8 21 22^ In addition, mental health problems have been found to adversely affect adherence to ART in this population, impacting clinical outcomes,^23 24^ with older adolescents (15–19) being the most affected.^24^ Despite the burden, the mental health needs of adolescents are often unaddressed; this is often perpetuated by low mental health awareness and literacy, limited access to mental health services as well inadequate services for adolescents and the cost of treating mental illnesses.^1 25 26^ Although an increasing number of studies have indicated a significant risk of poor behavioural outcomes that affect health and development in ALHIV, few evidence-based behavioural interventions exist to promote well-being and resilience in this population.^1721 27^,^29^ Well-being is the balance between an individual’s resource pool and the challenges they face while resilience refers to the capacity to maintain mental health despite exposure to adversity.^30 31^

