#### Study population

We will recruit adolescents (target sample size n=50) living with HIV and receiving care at AHRI-supported clinics. A random sample of 67 potential participants (ensuring gender balance) who are aware of their HIV status and have agreed to future contact with the AHRI team will be selected from the existing AHRI Demographic Information System (ACDIS) database, and they will be approached and invited to enrol. Adolescents will be included in the study if they are aged 16–19 at the time of recruitment, reside in uMkhanyakude at the time of recruitment, have a score of ≥10 on the Patient Health Questionnaire (PHQ-9) or Generalised Anxiety Disorder Scale (GAD-7) and provide informed consent. We will exclude individuals with a self-reported history of severe mental illness, including psychotic-related disorders, bipolar disorders, eating disorders and substance dependence, as well as those with cognitive deficits (assessed using the Mini-Mental Status Examination),^76^ those presenting with suicidal ideation or judged to be at active risk of suicide (as assessed using the Columbia-Suicide Severity Rating Scale), and those undergoing active psychiatric treatment (ie, on psychotropic medication or receiving formal psychotherapy).

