##### Intervention

After informed consent, eligible individuals will be screened using the PHQ-9 and GAD-7. Individuals with a score ≥10 on the PHQ-9 or GAD-7 will be enrolled in the study and will complete a set of baseline assessments (table 1). After completing the baseline assessment, they will be assigned a lay counsellor and a date for their first interaction. Only trained lay counsellors who have undergone the proposed 3-month training will deliver the adapted PM+Adherence intervention for seven sessions held once a fortnight over 4 months.

**Table 1 T1:** Assessment schedule

	Baseline (month 0) (t_0_)	End intervention (month 4) (t_1_)	Postintervention (month 6) (t_2_)
Demographics	X		
Viral suppression	X		X
Adherence	X	X	X
PHQ-9	X	X	X
GAD-7	X	X	X
Sleep disturbance	X	X	X
PROMIS	X	X	X
CYRM	X	X	X
PWS	X	X	X

CYRMChild and Youth Resilience MeasureGAD-7Generalised Anxiety Disorder ScalePHQ-9Patient Health QuestionnairePROMISPatient-Reported Outcomes Information System Sleep Disturbance ScalePWSPersonal Well-Being Score

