### Study outcomes

The primary outcomes of interest include (1) reach, which consists of how many of the approached ALHIV are enrolled in the study; (2) adoption and retention, which will assess the number of enrolled participants who attend ≥50% of sessions and undergo the final assessment at 6 months; (3) acceptability of the co-adapted intervention to determine how well the target population will receive the adapted intervention, the extent to which the intervention components meet the needs of the target population and the setting and (4) implementation, which will assess fidelity to the various elements of the intervention’s protocol, including consistency of delivery as intended as well as the adolescents’ use of the intervention strategies.

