### Data analysis

The primary outcome of this study is the feasibility and acceptability of the delivery of PM+Adherence among ALHIV in uMkhanyakude, KwaZulu-Natal. Feasibility will be determined using the following criteria: (1) reach will be assessed through 75% recruitment and consent rates; (2) adoption and retention, where enrolled participants attend ≥50% of sessions and complete assessments at 6 months; (3) implementation, where there is at least 75% fidelity to the protocol; (4) acceptability of the intervention will be assessed through semistructured interviews (see table 2). The proportion and 95% CI for each measure will be calculated.

**Table 2 T2:** Feasibility and acceptability measure

	Explanation	Time point	Criteria
Reach	Percentage of acceptance rate and number of adolescents recruited.	Baseline	At least 75% of the target population.
Adoption	Attendance of study participants to sessions and assessments throughout the trial.	During implementation	At least ≥50% of sessions attended.
Retention	Participants retention rates.	After implementation	A rate of 90% of participants attend the final assessment at 6 months.
Implementation	Through fidelity checklists, the research team will assess the adherence rate to the intervention protocol, including consistency of delivery as intended and the adolescents’ use of the intervention strategies.	During implementation	At least 75% or greater.
Acceptability of adapted intervention	Semistructured interviews assessing views of adolescents, facilitators and healthcare providers about the adapted intervention and implementation.	After implementation	Qualitative data will be coded for themes.

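### The step from 67 approached to 50 enrolled allows for willingness only and leaves out the PHQ-9/GAD-7 entry screen and the exclusions

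*Protocol article*

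**What the plan says.** **Who is approached.** Phase 3, Study population: "A random sample of 67 potential participants (ensuring gender balance") is drawn from the ACDIS database. The conditions on the draw are awareness of HIV status and agreement to future contact. Symptoms play no part in it.

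**Who is enrolled.** Study procedures, Intervention, places the symptom screen after consent: "Individuals with a score ≥10 on the PHQ-9 or GAD-7 will be enrolled in the study". Study population lists the same threshold as an inclusion criterion. It also excludes self-reported severe mental illness, cognitive deficit, suicidal ideation or active risk, and active psychiatric treatment.

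**How 67 and 50 are linked.** Sample size starts from a willingness assumption, "If the true proportion of those willing to enrol (reach) is 75" per cent, and concludes that "a sample size of 67 approached and 50 enrolled would allow us to estimate this proportion with a precision of ±10" per cent. It then gives ±8% for retention, based on 50 enrolled and 90% completing.

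**How reach is defined.** There are four descriptions:

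- Study outcomes: "reach, which consists of how many of the approached ALHIV are enrolled in the study".
- Sample size: the proportion willing to enrol.
- Data analysis: "reach will be assessed through 75% recruitment and consent rates".
- Table 2: the acceptance rate and the number recruited, judged against 75% of the target population.

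**The concern.** The sample-size statement treats a consenting adolescent as an enrolled one. Under the article's own procedures these differ, because a consenter who scores below 10 on both scales, or meets an exclusion, is not enrolled. The calculation has no term for that loss.

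Two things depend on it. The first is the enrolled sample of 50, and with it the stated retention precision. The second is a primary feasibility outcome. If reach is enrolled over approached, adolescents who agree but are not distressed count against it, and a well-accepted intervention could be recorded as missing its reach criterion because of how common symptoms are. If reach is willingness or acceptance, symptom prevalence does not enter. The article uses both readings.

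**Working it through.** **Inputs from the article.** Willingness c = 75%; 67 approached; 50 enrolled; retention 90%; 95% confidence intervals (Data analysis: "The proportion and 95% CI for each measure will be calculated").

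**Input not in the article.** The share s of consenters who score at least 10 on PHQ-9 or GAD-7. It is an assumption throughout and is shown as a range.

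**Step 1: reproduce the stated figures.** The half-width is 1.96 × √(p(1−p)/n).

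- 50 / 0.75 = 66.7, rounded up to 67; 67 × 0.75 = 50.25.
- Reach: 1.96 × √(0.75 × 0.25 / 67) = 0.104, against the stated ±10%.
- Retention: 1.96 × √(0.90 × 0.10 / 50) = 0.083, against the stated ±8%.

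Both reproduce. The ±10% has the 67 approached as its denominator; the ±8% has the 50 enrolled.

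**Step 2: add the screen.** Before exclusions, expected enrolled = 67 × 0.75 × s; enrolled/approached = 0.75 × s; number to approach for 50 enrolled = 50 / (0.75 × s), rounded up. The last column is the exact binomial probability of at least 50 enrolled out of 67 with success probability 0.75 × s.

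| s (assumed) | Enrolled from 67 | Enrolled/approached | Approach for 50 | P(≥50 of 67) |
|---|---|---|---|---|
| 30% | 15.1 | 22.5% | 223 | below 0.0001 |
| 50% | 25.1 | 37.5% | 134 | below 0.0001 |
| 70% | 35.2 | 52.5% | 96 | 0.0002 |
| 90% | 45.2 | 67.5% | 75 | 0.13 |
| 100% | 50.3 | 75% | 67 | 0.59 |

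Only the last row matches the article. The exclusions lower every row further.

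**Step 3: a rough proxy.** The only prevalence in the article is in the Introduction: "high rates of mental health problems, at a prevalence of 8%–12" per cent. It concerns mental health problems in general and is not a rate of scoring 10 or more on either scale. Used only as a proxy, it gives 67 × 0.75 × 0.08 = 4.0 to 67 × 0.75 × 0.12 = 6.0 enrolled, and 50 / (0.75 × 0.12) = 556 to 50 / (0.75 × 0.08) = 834 to approach.

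**Step 4: retention precision.** At 25 enrolled (s = 50%), 1.96 × √(0.09 / 25) = 0.118, about ±12 points instead of ±8.

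**Step 5: reach with full consent.** If every adolescent agrees, expected enrolled/approached equals s, less exclusions. Meeting 75% in expectation then needs about 75% of an unselected sample to screen positive. At s = 50%, 67 × 0.50 = 33.5 would be enrolled, and the chance of 50 or more is about 0.00003. At s = 70% that chance is 0.25.

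**The case against.** **The arithmetic is right.** This stands. Both half-widths reproduce and 50 / 0.75 does give 67. The fault is a missing yield term, not a miscalculation.

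**A reader might infer that 67 approached cannot give 50 enrolled, or that reach must miss 75%.** The article does not support either, because it gives no screen-positive rate. At 75% consent and 90% positive the chance of 50 or more is 0.13; with full consent and 70% positive it is 0.25. The supportable statement is that 50 is not to be expected unless nearly all consenters screen positive.

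**A reader might take 8%–12% as the protocol's own eligibility rate.** It is background from other South African studies, cited without instrument, cut-off or age band, and no design calculation uses it. The figures of 4–6 enrolled and 556–834 approached are therefore illustrative. The finding does not need them, since even 90% positive leaves an expected shortfall.

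**Reach may mean only willingness or acceptance.** On the Sample size wording, and on the acceptance rate in Table 2, prevalence does not affect the criterion. That is correct, and it limits the reach part of this point to the enrolled-over-approached definition in Study outcomes and the recruitment rate in Data analysis. The step from 67 to 50 enrolled is unsupported on either reading.

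**More could be approached, and the full protocol may say so.** No rule is stated that stops recruitment at 67, and an article may leave replenishment to the full document. If more are approached, the ±8% can be kept. But both Study population and Sample size state 67, and Sample size pairs it with 50 enrolled, so the stated figure still needs correcting.

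**Conclusion.** The concern holds in this form: the statement that 67 approached gives 50 enrolled omits the symptom screen and the exclusions, and is true in expectation only if every consenter screens positive and none is excluded. At 75% consent and assumed positivity of 30% to 90%, 67 approached gives about 15 to 45 enrolled, and 50 enrolled needs about 223 down to 75 approached, before exclusions. The retention precision of ±8% depends on actually enrolling 50.

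The reach criterion is affected only where reach means enrolled over approached, or recruited. There it is capped by symptom prevalence and could be missed at any level of willingness. Where reach means willing or accepting, it is not affected. The definitions need to be reconciled because they diverge at the point where screening follows consent. The true screen-positive rate is unknown from the article, so the size of the shortfall is a range and not an estimate.

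**What to change.** 1. Define reach once, as consented to screening divided by approached, in Study outcomes, Sample size, Data analysis and Table 2, and apply the 75% criterion to that ratio.
2. Report the screen-positive share, the eligible share and enrolled/approached descriptively, with no 75% target. A 75% target on enrolled among eligible would add little: symptom eligibility is known only after consent, so that ratio would be near 100% almost by construction.
3. Restate 67 as the number that gives about ±10% on the consent proportion, not as the number that yields 50 enrolled.
4. Choose one of two routes:
   - Keep 50 enrolled: approach sequentially from a randomly ordered ACDIS list until 50 are enrolled, and state the expected number approached as a range over labelled yield assumptions.
   - Keep 67 approached: restate the expected number enrolled and the retention precision over the same range.

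**Cost.** Items 1 to 3 are changes of wording. Keeping 50 means more approach, consent and screening work. Each approach involves an introduction and at least 48 hours for consideration, three research assistants are planned, and the article does not say how many adolescents in ACDIS could be approached. Keeping 67 costs no extra fieldwork, but the stated figures become less favourable. The reach definition should be settled before recruitment, because it fixes what counts towards a primary outcome.

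### Adoption, a primary feasibility criterion, is inconsistently defined, borrows its ±8% precision from 6-month retention, and has no required share of participants

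*Protocol article*

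**What the plan says.** The protocol article describes adoption in five places.

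- **Sample size:** adoption is equated with retention. The premise is "If 90% of participants complete the study at 6 months", and the conclusion is that "a sample size of 50 ALHIV will allow us to estimate adoption (participant retention) with a precision of ±8" per cent.
- **Drop-outs:** the adoption criterion is attendance of at least half of the sessions. Assessments are not mentioned.
- **Study outcomes:** adoption and retention form one numbered item, measured by "the number of enrolled participants who attend ≥50% of sessions and undergo the final assessment at 6 months".
- **Data analysis, text:** the pairing is repeated as "adoption and retention, where enrolled participants attend ≥50% of sessions and complete assessments at 6 months".
- **Data analysis, Table 2:** adoption and retention are separate rows. The adoption criterion is "At least ≥50% of sessions attended", although the explanation in the same row covers attendance at both sessions and assessments. The retention criterion is "A rate of 90% of participants attend the final assessment at 6 months".

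Table 2 also sets 75% for reach and 75% for implementation. Acceptability is assessed qualitatively. Data analysis adds that "The proportion and 95% CI for each measure will be calculated". The intervention has seven sessions.

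**The concern.** Adoption is one of the primary outcomes on which the study will judge whether PM+Adherence is fit for further testing, with a randomised trial foreseen. Two things stand in the way of that judgement.

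First, the only precision quoted under the name adoption is calculated from a different measure. A participant can attend most sessions and miss the month-6 assessment, or the reverse, so attendance and retention need not have the same rate or the same interval.

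Second, adoption is the only quantitative criterion without a cohort-level mark. The article says what one participant must do to count, but not how many of the 50 must do it. If attendance proves middling, the team would have to decide afterwards whether that is a pass, and whether to judge attendance alone or attendance combined with the final assessment.

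**Working it through.** **Inputs.** Enrolled sample: 50 (Study population, "We will recruit adolescents (target sample size n=50) living with HIV"). Assumed completion at 6 months: 90% (Sample size). Confidence level: 95%, two-sided; it is stated for the analysis in Data analysis and assumed here to apply to the precision figures too. Sessions: 7 (Intervention). The article assumes no attendance rate, so a range is shown.

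**Formula.** Half-width = 1.96 × √(p(1 − p)/n).

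**Step 1: reproduce the plan's figures.**
- Retention: 1.96 × √(0.90 × 0.10/50) = 0.083, or 8.3 points, matching the stated ±8%.
- Reach, as a check on the method: 1.96 × √(0.75 × 0.25/67) = 0.104, matching the stated ±10%.

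The plan's formula is therefore the one above, and ±8% is correct for a proportion of 90%.

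**Step 2: the per-person threshold.** 50% of 7 is 3.5, so a participant must attend at least 4 sessions.

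**Step 3: precision for adoption as attendance, n=50.**

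| Share attending at least 4 of 7 (assumed) | 95% half-width (points) |
|---|---|
| 50% | ±13.9 |
| 70% | ±12.7 |
| 80% | ±11.1 |
| 90% | ±8.3 |
| 95% | ±6.0 |

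The stated ±8% would apply to adoption only if attendance also happened to be about 90%.

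**Step 4: the joint reading.** If adoption means attending at least half of the sessions and also completing month 6, its rate cannot exceed the retention rate. With 90% retention and an assumed, independent 80% attendance, it is 0.90 × 0.80 = 72%, with half-width 1.96 × √(0.72 × 0.28/50) = 12.4 points. Without independence, the same two margins allow anything from 0.90 + 0.80 − 1 = 70% (±12.7) to 80% (±11.1). It reaches 90% ±8.3 only if everyone who completes month 6 also meets the attendance threshold.

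**Step 5: the pass marks side by side.**

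| Criterion | Required level |
|---|---|
| Reach | 75% |
| Retention | 90% |
| Implementation (fidelity) | 75% |
| Adoption | at least half of sessions per participant; share of participants not stated |

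**The case against.** The strongest defence is that most of the article is consistent. The items in Study outcomes and Data analysis are headed adoption and retention together, and their two clauses can be taken one for each term: sessions for adoption, the 6-month assessment for retention. Read that way, they agree with Drop-outs and with the criteria in Table 2. This stands as a possible reading, so it would be too strong to say the article gives three incompatible definitions. It does not rescue the Sample size section, which names adoption as retention while Table 2 keeps them apart. Nor does it settle the adoption row of Table 2, whose explanation counts assessments while its criterion does not.

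A second defence is that ±8% is conditional on 90%, glossed as retention, and correctly computed. That also stands. A reader might infer a miscalculation, but the fault is in the label. Nothing in the article shows that attendance would fall below 90%, and above 90% the interval would be narrower.

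A third defence is that a journal article condenses a fuller protocol, which may hold the missing share. But the article itself includes a criteria table that gives numeric marks to the other quantitative measures, and its own sections disagree on what adoption is.

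Two further inferences are tempting but unsupported. Table 2 taken alone might suggest average attendance of 50% across the cohort; Study outcomes counts participants who reach the threshold, which contradicts that. One might also argue that half of the sessions is too lenient because two of the seven are adherence-focused; that is a preference, and nothing in the article conflicts with the chosen threshold.

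**Conclusion.** The point holds in a limited form. The precision stated for adoption is the precision of 90% retention: 8.3 points, correct for that measure and mislabelled. For adoption as attendance, the half-width with 50 participants would be ±11.1 points at 80%, ±12.7 at 70% and never more than ±13.9. These rates are assumptions, because the article gives none, and the joint figure of 72% ±12.4 rests on assumed independence as well.

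The per-person threshold is stated; what is missing is the share of participants who must meet it. A reader might conclude that the whole primary outcome cannot be judged, but that goes too far. Retention has its 90% target, reach and implementation have theirs, and an attendance proportion with a 95% CI can be reported once one definition is chosen. Only the pass or fail verdict on adoption is undetermined. The sample size and design are not called into question.

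**What to change.** Use one set of definitions in Drop-outs, Study outcomes, Sample size, Data analysis and Table 2, with all enrolled participants as the denominator:

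- **Adoption:** attended at least 4 of 7 sessions (the plan's own 50% rule), with a required share of participants fixed before data are seen. The team should choose and justify that share.
- **Retention:** month-6 assessment completed, target 90% as now.
- **Joint measure**, if wanted: both conditions met, descriptive only.

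In Table 2, remove assessments from the explanation of adoption so that it matches its criterion. In Sample size, attach ±8% to retention only, and give adoption's precision at its own assumed rate, for example ±11.1 points at 80% or ±12.7 at 70%, with ±13.9 as the ceiling.

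The cost is wording in those places and one prespecified number. No new data are needed, since session attendance and month-6 completion are already study measures. The downside is that the stated precision for adoption may look less favourable than ±8%.
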